**Fig. 2 Fig2:**
[figure not shown]
Schedule of volunteers’ enrolment, interventions, and assessments according to the SPIRIT statement. AMX, amoxicillin; Mo, months; MTZ, metronidazole

The administration of all medications (probiotic and antibiotics) and placebos starts immediately after the first SRP session. Antibiotics (or placebos) are given TID for 14 days and include two tablets, one of MTZ and one of AMX. Antibiotics and placebos are being specially prepared for this study by the same pharmacy (*Gallen Pharmacy and Manipulation* Ltda, Maringá, PR, Brazil). All tablets have the same color and size and are stored in properly coded opaque plastic bottles, containing 22 capsules/lozenges. Volunteers, therapists, and examiners are blind to the interventions applied.

Probiotic (or placebo) are administered two times per day for 90 days and include one lozenge every 12 h after brushing and flossing. The second lozenge is administered just before going to sleep. The lozenges are slowly dissolved in the volunteer’s oral cavity. Probiotic and placebo are being prepared for this study by *BioGaia AB* (Stockholm, Sweden). Probiotic lozenges contain 2 different strains of *Lactobacillus reuteri*: *L. reuteri* DSM 17938 and *L. reuteri* ATCC (PTA 5289), each at a minimum amount of 1 × 10^8^ CFU per lozenge. Placebo probiotic lozenges are identical to the active lozenges in taste, texture, and shape, but they do not contain *L. reuteri*. All lozenges are kept refrigerated at a temperature below 25 °C until they are handed to the patient.

SRP is performed using Gracey curettes (conventional and mini-fives) 5/6, 7/8, 11/12, and 13/14 under local anesthesia, and the treatment is completed in four to six sessions of approximately 1 h, distributed over a period of 14 days. At the end of each session, the clinical coordinator of each center evaluates the effectiveness of SRP using the outcome “smoothness of the scaled roots.” All volunteers will receive clinical monitoring at baseline and at 3, 6, and 12 months post-therapies. In addition, all subjects will receive periodontal maintenance every 3 months post-treatment until the end of the study. These sessions include OHI and supragingival/subgingival biofilm/calculus removal, as necessary. If any participant shows periodontal attachment loss ≥ 2 mm in 3 or more sites during the maintenance phase, they will be excluded from the study and referred for periodontal re-treatment.

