### Primary and secondary outcome variables

The primary outcome variable is the difference among groups for the percentage of volunteers achieving the clinical endpoint for therapy (≤ 4 sites with PD ≥ 5 mm) at 1 year post-treatment [57].

Secondary outcome variables are as follows: difference between baseline and 12 months post-therapy for mean CAL gain and PD reduction (in the full mouth and in different PD categories), mean number and percentage of volunteers with 0, 1–2, or ≥ 3 sites with different thresholds of residual pockets (e.g., PD ≥ 6 and ≥ 7 mm) at 12 months post-therapy; mean number (and mean reductions) of different thresholds of residual pockets at all post-treatment time points; difference among groups for the percentage of volunteers achieving different thresholds of BOP (e.g., ≤ 10%, 20% and 30% of bleeding sites in the mouth) at 1 year post-treatment; differences in the occurrence of adverse events among therapeutic groups; and differences in the counts and proportions of 40 bacterial species in the biofilm samples at all post-treatment time points and in the levels of 17 chemokines in the GCF and peripheral blood samples at 1 year post-therapy.

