### Sample size calculation

The ideal sample size to assure adequate power for this study was based on the percentage of volunteers achieving “≤ 4 sites with PD ≥ 5 mm” at 1 year post-treatment [57]. Considering a difference of 44 percentage points between groups for volunteers achieving this clinical endpoint at 1 year post-treatment [5] and a significance level of 5%, 17 subjects per group would be necessary to provide a power of 80%. Considering an attrition of 25%, it was established that at least 22 subjects should be included in each treatment group. Considering a difference of 30 percentage points between groups for volunteers achieving this clinical endpoint at 1-year post-treatment and a significance level of 5% 37 subjects per group would be necessary to provide a power of 80%. Considering an attrition rate of 15%, it was established that 44 volunteers should be included in each treatment group (total 176 subjects).

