### Statistical analysis

#### Clinical monitoring

The chi-square test will be used to compare the differences in the frequency of gender and to compare the differences in the frequency of subjects achieving the clinical endpoint for treatment (≤ 4 sites with PD ≥ 5 mm) at 1-year (primary outcome variable) and of self-perceived adverse effects. Each individual continue/categorical variable will be computed per subject and then across subjects in each group. The significance of clinical differences over the course of the study will be sought using repeated measures ANOVA or Friedman multiple comparison tests (and their respective post-hoc tests, when necessary), and at each time point (among groups), using either ANOVA or Kruskal-Wallis multiple comparison tests (and their respective post-hoc tests when necessary) or ANCOVA with adjustments for the baseline values. Parametric or non-parametric tests will be chosen based on the normality of the data. A stepwise forward logistic regression analysis will be performed to investigate the impact of predictor variables on the clinical endpoint for treatment, i.e., “presence of ≤ 4 sites with PD ≥ 5 mm at 1-year post-therapy (yes/no).” The Number Needed to Treat (NNT) with each treatment protocol in order to obtain treatment success (≤ 4 sites with PD ≥ 5 mm) will be calculated using the following formula: NNT = 1/ARR, where ARR = |CER − EER| and CER = control group event rate and EER = experimental group event rate (http://ktclearinghouse.ca/cebm/glossary/nnt). The level of significance will be set at 5%. The data will be evaluated using intention-to-treat analysis with last observation carried forward.

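### Participants withdrawn for attachment loss can be counted as 1-year successes, because last observation carried forward fills their endpoint with an earlier probing-depth result

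*Protocol article*

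**What the plan says.** Three statements in the protocol article have to be read together.

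- **Exit rule** (Interventions, text after Figure 2): "If any participant shows periodontal attachment loss ≥ 2 mm in 3 or more sites during the maintenance phase", then "they will be excluded from the study and referred for periodontal re-treatment".
- **Primary outcome** (Primary and secondary outcome variables): the comparison among groups of the "percentage of volunteers achieving the clinical endpoint for therapy (≤ 4 sites with PD ≥ 5 mm) at 1 year post-treatment".
- **Analysis rule** (Statistical analysis, Clinical monitoring): "The data will be evaluated using intention-to-treat analysis with last observation carried forward".

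The examinations that can supply a carried value are set in Interventions: "All volunteers will receive clinical monitoring at baseline and at 3, 6, and 12 months post-therapies". Maintenance runs alongside: "all subjects will receive periodontal maintenance every 3 months post-treatment until the end of the study". Nothing in the article says how a participant withdrawn under the exit rule is scored on the primary outcome.

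**The concern.** The exit is not an administrative loss. It happens because the disease has progressed after treatment, so it carries information about the outcome. Last observation carried forward (LOCF) ignores that information and replaces the missing 1-year status with whatever the last PD examination showed. If that examination had no more than 4 sites at 5 mm or deeper, someone who left because of progression and was sent for re-treatment enters the primary analysis as a success at 1 year.

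The success rates are the raw material of the chi-square test on the primary outcome, the stepwise logistic regression and the NNT. With 44 participants per arm, a few misclassified exits can move all three.

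LOCF also gives one rule two meanings for ordinary dropouts, depending on when they leave.

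**Working it through.** **1. Can a withdrawn participant be scored as a success?**

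| | Exit rule | Primary endpoint |
|---|---|---|
| Measure | attachment loss of 2 mm or more | PD of 5 mm or more |
| Threshold | 3 or more sites | success if 4 sites or fewer |
| When | any time in maintenance | 1 year |

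There are two routes to a carried success.

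- *Different measure.* Attachment can be lost without the site reaching PD 5 mm, for example through recession. Even an examination made when the progression is found may meet the PD endpoint.
- *Earlier value.* Full examinations are at baseline and months 3, 6 and 12, while maintenance is every 3 months. For an exit at month 9 the carried value is the month-6 one, recorded before the progression was found.

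The result is possible, not automatic. An exit whose last examination shows 5 or more sites at PD 5 mm or deeper is carried as a failure.

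**2. Does the other reading help?** If the exclusion meant removal from the analysis, participants would be dropped because of their outcome. That contradicts the stated intention-to-treat analysis and still does not count them as failures.

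**3. The plan's own sample size.** 37/(1 − 0.15) = 43.5, so 44 per group, and 4 × 44 = 176. This reproduces. The arm rates behind the 30-point difference are not stated. A two-sided 5% test at 80% power without continuity correction gives exactly 37 for control rates of 16–17% or 53–54%.

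**4. Weight of one participant.** 1/44 = 2.3 percentage points of that arm's success rate.

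**5. Effect on the comparison (illustration).** The article gives neither arm rates nor an expected number of exits, so both are assumed here. True rates are 25% against 55%, with 44 per arm and a two-sided 5% test. Observed rate = true rate + k/44, where k is the number of exits carried as successes; NNT = 1/difference.

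| k control | k test | Observed rates | Difference | NNT | Power |
|---|---|---|---|---|---|
| 0 | 0 | 25.0% v 55.0% | 30.0 | 3.33 | 83% |
| 2 | 2 | 29.5% v 59.5% | 30.0 | 3.33 | 82% |
| 3 | 1 | 31.8% v 57.3% | 25.5 | 3.93 | 68% |
| 4 | 0 | 34.1% v 55.0% | 20.9 | 4.78 | 50% |
| 0 | 3 | 25.0% v 61.8% | 36.8 | 2.72 | 95% |

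Other assumed rates show the same pattern. For the rows (0, 0), (3, 1) and (4, 0), power is 92%, 75% and 58% at 10% v 40%, and 82%, 68% and 50% at 35% v 65%. The differences and NNTs do not change, because the true difference is 30 points in each case.

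**6. Other dropouts.** Entry requires at least 6 teeth, each with an interproximal site at PD 5 mm or deeper. Every baseline therefore has at least 6 such sites, and 6 > 4 is a failure. A participant lost before month 3 is always imputed as a failure. One lost later is imputed as early status standing in for 12-month status.

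**The case against.** The best defence is that the exclusion stands in Interventions, beside referral for re-treatment, and most naturally means the end of study follow-up. On that reading the participant stays in the analysis and intention-to-treat is not breached. That is fair. A reader might infer that the plan drops these patients and so violates its own principle, but with LOCF supplying a value the document does not say so. The breach arises only on the alternative reading. What remains is how the retained participant is scored.

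The defence can add that a participant with attachment loss but few deep pockets does meet the endpoint as written, so scoring the exit as failure changes the definition. This stands in part: it is a composite definition and should be stated as one. But the endpoint is status at 1 year, and an earlier examination before re-treatment does not show that status.

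Two stronger inferences are tempting and should not be drawn.

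- *The site counts prove the error.* Setting 3 sites for exit against 5 for failure compares attachment loss with PD. The mismatch of measures and the earlier timing make misclassification possible; the two counts alone prove nothing.
- *Carry-forward favours the lozenges.* The month-3 visit falls near the end of the 90-day course, but no passage says the effect fades, placebo arms also carry early values, and an exit at month 9 carries month 6.

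Finally, a condensed article may leave missing-data detail to a fuller document. Here, however, the article states the rule, without exception, and the stated rule is the problem.

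**Conclusion.** The point holds. As written, the exit rule and LOCF together allow a participant withdrawn for progression to count as a 1-year success, and nothing else in the article prevents it.

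The firm figure is 2.3 percentage points of an arm's success rate per such participant. The number of exits and the direction of bias between arms cannot be known from the document. More misclassified exits in the control arm shrink the difference and raise the NNT; more in a test arm do the reverse; equal numbers leave the difference alone but overstate every success rate. The differences, NNTs and power in the table rest on assumed arm rates and exit numbers and show sensitivity only.

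A reader might take the planned 15% attrition as the exit share and set the resulting inflation against the 30-point planned difference. The document does not support that: 15% is an allowance for attrition in general, and inflation of one arm's rate is not bias in a difference between arms.

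The inconsistent handling of other dropouts is a second, smaller weakness of the same rule.

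**What to change.** Leave the clinical re-treatment rule exactly as it is and change the analysis text before unblinding.

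1. State that participants withdrawn under the attachment-loss rule remain in the analysis set and count as not achieving the 1-year endpoint. Say in Interventions that the exclusion refers to study follow-up, not to the analysis.
2. For other missing 12-month results, replace LOCF with multiple imputation using arm, centre, and the baseline, 3-month and 6-month counts of sites with PD of 5 mm or more.
3. Add a sensitivity analysis in which every missing 12-month result counts as not achieved.
4. Use the same status in the chi-square comparison, the logistic regression and the NNT.

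The cost is a few sentences and some analysis code, including a way to combine the group comparison over imputed data sets. No new participants or visits are needed and the sample size is unchanged. Reported success rates may be slightly lower.

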#### Microbiological and immunological monitoring

Microbiological data will be expressed in counts (levels) and proportion counts of DNA probes. Mean counts will be expressed as counts × 10^5^. Microbial data will be calculated at each site for each volunteer and then across volunteers within each group, at each time point. The sum of the mean proportions of individual bacterial species will be computed for each microbial complex described by Socransky et al. [58]. The concentration and total amount of each cytokine/chemokine in the GCF will be assessed per volunteer and then per volunteer within each group at each study time point. Immunological data will be calculated at each site for each volunteer and then across volunteers within each group, at each time point. The significance of differences in microbiological and immunological parameters over the course of the study will be sought using repeated measures ANOVA or Friedman multiple comparison tests (and their respective post-hoc tests, when necessary) and at each time point (among groups) using either ANOVA or Kruskal-Wallis multiple comparison tests (and their respective post-hoc tests when necessary) or ANCOVA with adjustments for the baseline values. Parametric or non-parametric tests will be chosen based on the normality of the data.

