### Microbiological monitoring (baseline, 3, 6, and 12 months)

#### Sample collection

Nine subgingival samples are being collected per volunteer, three in each of the following categories: shallow (PD ≤ 3 mm), moderate (PD = 4–6 mm), and deep (PD ≥ 7 mm). The selected sites are located on non-contiguous interproximal teeth, preferably distributed across the four quadrants and subset according to baseline PD. Teeth with open margins and overhangs, furcation lesions, extensive caries, and/or endo-periodontal lesions are not selected for sampling. After recording the clinical parameters, supragingival plaque is removed and the subgingival samples are collected with individual sterile mini-Gracey curettes #11–12, positioned at the most apical portion of the subgingival sulcus/pocket and with a single apical-coronal movement. The samples are immediately placed in separate Eppendorf tubes containing 150 ul of TE buffer solution (10 mM Tris-HCl, 1 mM EDTA, pH 7.6), and then 100 ul of 0.5 M NaOH is added to each tube and the samples are dispersed using a vortex mixer. The samples are being stored at − 20 °C. The tubes containing the samples are previously identified with the volunteer’s code, date, and site collected.

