### Immunological monitoring (baseline and 12 months)

#### Serum and GCF sampling

Peripheral blood samples and GCF are being collected 1 week after clinical examination. Two non-contiguous diseased sites (i.e., PD and CAL > 5 mm, BoP and no furcation involvement) and two non-contiguous healthy sites (i.e., PD and CAL < 4 mm without BOP and/or gingival bleeding) are being randomly chosen per patient for GCF sampling (among the same sites selected for microbiological sampling). After removal of the supragingival biofilm, the selected sites are isolated with cotton rolls and gently dried with an air syringe to eliminate saliva. GCF is collected by inserting standard paper strips (Periopaper, Oraflow Inc., Smithtown, NY, USA) up to approximately 2 mm into the sulcus/pocket for 30 s. Strips visually contaminated with blood are discarded. The GCF volume is measured in a calibrated device (Periotron 8000, Proflow Inc., Amityville, NY, USA), and the readings are converted into an actual volume (microliter, μl) by reference to a standard curve. Strips from the four selected sites are immediately placed into separate microcentrifuge tubes and stored at − 80 °C for subsequent assays. Peripheral blood samples are into an appropriate tube (Serum BD Vacutainer Plus Plastic Serum Tubes, BD, Franklin Lakes, NJ). Fasted samples are obtained in the morning for all patients. Immediately after blood collection, the serum is separated from blood by centrifugation (10 min at 1300 rpm) and stored in aliquots at − 80 °C.

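### Cytokines are measured only twice, so the planned Friedman test of within-arm change is a sign test that ignores the size of each patient's change; a paired test should be named instead

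*Protocol article*

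**What the plan says.** The protocol article samples the two laboratory data sets on different schedules. One heading reads "Microbiological monitoring (baseline, 3, 6, and 12 months"), which is four occasions. The other reads "Immunological monitoring (baseline and 12 months"), which is two.

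Under Statistical analysis, the subsection on microbiological and immunological monitoring treats both alike: "The significance of differences in microbiological and immunological parameters over the course of the study will be sought using repeated measures ANOVA or Friedman" tests, with post-hoc tests when necessary. The choice of branch is stated as "Parametric or non-parametric tests will be chosen based on the normality of the data". No separate test is named for data with two occasions, and no transformation is mentioned.

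Comparisons between arms are a separate matter. They are made "at each time point (among groups) using either ANOVA or Kruskal-Wallis multiple comparison tests", or by ANCOVA adjusted for baseline. The secondary cytokine outcome is worded as differences "in the levels of 17 chemokines in the GCF and peripheral blood samples at 1 year post-therapy".

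**The concern.** Friedman's test is meant for three or more related measurements. With two, it keeps only the direction of each patient's change. A patient whose level falls by 80% and one whose level falls by 2% count the same. The rule suits the microbiology, but applied to the cytokines it replaces the usual paired tests with a coarser one.

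At stake is the power of the within-arm baseline to 12-month tests wherever the non-parametric branch is used. The rule covers every analyte in serum, and in crevicular fluid both as concentration and as total amount, in four arms.

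**Working it through.** **Inputs.** Two cytokine occasions and four microbiological occasions (section headings). Patients per arm: 37 evaluable, 44 enrolled after 15% attrition (Sample size calculation; 37/0.85 = 43.5, rounded up to 44). Significance level 5%, taken as two-sided. The article states no power or effect size for cytokines, so there is no figure of its own to reproduce.

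**Step 1: what Friedman becomes with two occasions.** With k = 2 and n patients,

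Q = 12/(n·2·3) × (R1² + R2²) − 3n·3 = (2/n)(R1² + R2²) − 9n.

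The rank sums satisfy R1 + R2 = 3n. Write d = R1 − R2. Without ties, |d| is the number of patients who rose (n+) minus the number who fell (n−). Then R1² + R2² = (9n² + d²)/2 and

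Q = 9n + d²/n − 9n = (n+ − n−)²/n,

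which is the sign-test chi-square. On 500 simulated data sets the two agreed to within 5 × 10⁻¹⁴. If m pairs are tied, the tie-corrected form is (n+ − n−)²/(n − m), the sign test on the untied pairs.

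Because ranking is within patient, Friedman gives the same answer on raw and log levels. The parametric branch has no such problem: repeated measures ANOVA with two occasions is the paired t test.

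**Step 2: large-sample efficiency of the sign test against Wilcoxon signed-rank.** The formula is f(0)²/[3(∫f²)²], where f is the density of the paired changes about their centre.

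| Distribution of changes | Efficiency | Loss |
|---|---|---|
| Uniform | 0.333 | 67% |
| Normal | 0.667 | 33% |
| Logistic | 0.750 | 25% |
| t, 5 df | 0.774 | 23% |
| t, 3 df | 0.853 | 15% |
| Laplace | 1.333 | none (a gain) |

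The normal row is like analysing 44 × 2/3 ≈ 29 patients instead of 44.

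**Step 3: log-normal levels, signed-rank on raw differences.** Power was simulated at n = 37 under three assumed pairs of between- and within-patient log SDs. Efficiency follows from [(1.96 + z of sign power)/(1.96 + z of signed-rank power)]².

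- SDs 1.0 and 0.7: 60.7% v 68.4%; (2.231/2.439)² = 0.84, loss 16%.
- SDs 0.7 and 0.5: 60.9% v 71.4%; (2.237/2.525)² = 0.78, loss 22%.
- SDs 1.2 and 1.0: 60.4% v 66.5%; (2.224/2.386)² = 0.87, loss 13%.

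**Step 4: power in a concrete case.** Assumed: log-normal levels, correlation 0.5 between visits, a true 35% fall, 20,000 replicates.

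| n, SD of log | Friedman | Signed-rank, raw | Signed-rank, log |
|---|---|---|---|
| 37, 1.0 | 53% | 63% | 70% |
| 44, 1.0 | 61% | 71% | 78% |
| 44, 1.5 | 32% | 37% | 44% |

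With no true change and SD 1.0, all three reject about 5% of the time. In the first row, replacing Friedman gains about 10 points; the further 7 or so come from the log scale, which the article does not plan.

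**Step 5: would Friedman be selected?** The article reports cytokines in pg/site, pg/µl and pg/ml, so a natural reading is that normality is judged on raw values. In the SD 1.0 cases, Shapiro-Wilk at 5% rejected normality of raw levels in over 99% of data sets and of raw differences in about 88-96%. Friedman would then be used even though the log changes are exactly normal.

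**The case against.** The strongest objection concerns size. A reader might infer that the plan always discards a third of the information. The documents do not support that. One third is the loss when changes are normal, and the article sends data judged normal to repeated measures ANOVA, which loses nothing. The objection stands against a fixed figure, but not in full: for log-normal levels judged on the raw scale, Friedman is chosen although a log-scale analysis would be well behaved, and the one-third loss then applies. No distribution is given, so neither case can be asserted.

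A reader might also infer that real changes would be reported as absent. That does not follow from power of 61% against 71% with the 5% level held.

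Nor do the treatment comparisons suffer. The 1-year cytokine outcome is compared among arms by ANOVA, Kruskal-Wallis or ANCOVA. All arms receive scaling and root planing, so change within an arm does not by itself answer the adjunctive question.

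The mention of post-hoc tests is no fault either: they are to be used when necessary, and with two occasions they are not.

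The sign test is valid and, unlike signed-rank read as a test of location, does not need symmetric changes. That stands, so the complaint is about efficiency and not error rates.

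Finally, a journal article condenses the plan, and a full analysis plan might name paired tests. But the article does not leave this open: it names a test for these data, and that test fits only the other data set.

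**Conclusion.** The point holds in a limited form. The reduction of Friedman to the sign test at two occasions is exact. It usually costs power against a paired rank test: up to about one third of efficiency if log changes are near normal and the comparator is run on logs, roughly 13-22% against signed-rank on raw log-normal levels, and nothing for Laplace-type tails. In the assumed case with a log SD of 1.0, signed-rank on raw levels gains about 10 points of power. With a log SD of 1.5 it gains about 5.

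These sizes depend on assumed distributions, correlation and effect. The consequence is confined to supportive within-arm change tests of a secondary outcome. The change is worth making because it is nearly free.

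**What to change.** In the statistical subsection on microbiological and immunological monitoring, limit Friedman and its post-hoc tests to the four-visit microbiological data. For the immunological data, add for example: *Within each arm, the change from baseline to 12 months will be tested with a paired t test if the changes are approximately normal and otherwise with the Wilcoxon signed-rank test, preferably on log-transformed levels; the estimated change will be reported with its 95% confidence interval.*

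State also the scale on which normality is judged, and the value assigned to results below the detection limits listed under Processing of serum and GCF samples, since the log scale needs one.

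The cost is a sentence or two, with no new data, patients or procedures. The small downside is that signed-rank, read as a test of location, assumes roughly symmetric changes; the log scale often helps with that but does not guarantee it.
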